### Intervention Zones

The Newhints intervention as described above was implemented in the 49 intervention zones. All pregnant women and newborns living in these zones were therefore potential recipients of the intervention receiving home visits from CBSVs, in addition to routine maternal and child health (MCH) care currently available.

### Control Zones

Pregnant women and newborns living in the control zones continued to benefit from the routine MCH care currently available, which includes: antenatal clinics (ANC), Infant Welfare Clinics (IWC), access to free delivery with skilled attendants, access to TBA delivery and care, and routine interactions with CBSVs concerning outreach MCH and immunisation clinics. In addition control zones benefitted from the hospital essential newborn care strengthening and health facility sensitisation that covered all facilities in the trial area.

### Sample size

The sample size was determined by the primary outcome, all cause neonatal mortality, using the baseline neonatal mortality rate (NMR) of 31 per 1000 live births and the intraclass correlation coefficient (ICC) of 0.0007256, where the ICC[14] is defined as the ratio of the between zone variation to the total variation. This suggests that a total sample size of 15,200 livebirths would have 80% power to detect a 25% reduction in NMR at the 5% significance level, 93% power to detect a 30% reduction and 60% power to detect a 20% reduction. This sample size should be achieved by the number of livebirths that take place in a year in the trial area. The evaluation will be based on data collected for all babies born from 1 January 2009; this is 1 month after the intervention was fully implemented, and 6 months after CBSVs started assessing babies in July 2008 as well as counselling about newborn care practices.

### Impact evaluation

The primary outcomes are all cause neonatal mortality and key care practices; these will be compared between intervention and control zones. Secondary outcomes are age and cause-specific neonatal mortality. All required data are being collected through the surveillance system of 4-weekly home visits to all women of reproductive age established for the ObaapaVitA vitamin A and maternal mortality trial that took place from December 2000-October 2008[15]. This surveillance has been continued for the Newhints trial.

Resident fieldworkers are responsible for a fieldwork area (FWA) of four contiguous clusters of compounds, visiting women in one cluster per week over a 4-weekly cycle. Each week, fieldworkers receive an updated listing of women to be visited that week, and their pregnancy status, arranged by compound. A MONTH form is completed for each woman, and includes questions on whether she was present, if not whether she had died, any morbidity requiring treatment outside the home or hospitalisation, her pregnancy status, and a question on the outcome of the pregnancy, completed when a pregnancy ends. There is a scheduled 4-week fieldwork break each year over Christmas.

Other forms are completed as required. A PROFILE form collecting socio-demographic information is completed as soon as a woman reports that she is pregnant. A birth results in: a BIRTH form collecting data on pregnancy, delivery, the baby (or babies), newborn care practices and contact with CBSVs; and monthly INFANT form(s) completed until the baby reaches 12 months of age collecting data on their status, and exposure to key child survival interventions. These forms were revised to ensure that they capture data on practices promoted by the Newhints intervention.

Verbal post-mortems (VPMs) are carried out for all neonatal deaths in the trial area. A surveillance supervisor visits the household and interviews the mother or care-taker about the circumstances surrounding the death, including an open history, and specific questions on symptoms. All VPMs are reviewed by two experienced doctors, who independently code the likely cause of death. If they disagree, the form is reviewed by a third doctor; if their diagnosis matches one of the other two, this is accepted. If not, they meet to discuss the case and attempt to reach agreement. If this is not possible the cause is coded as unable to be determined.

#### Data Management

The trial impact evaluation outcomes will be derived from the surveillance database which was established in 2000 using Visual FoxPro (version 6.0 Microsoft Corp Seattle WA USA), and which was modified to include new data collection forms developed for Newhints. All forms are manually checked for completeness and consistency before they leave the field, collected and processed on a weekly basis. Independent double data entry with verification is carried out together with range and consistency checks, and inter-table consistency checks. Any queries identified are resolved promptly by the trial management team, and the database updated. New data are added to the database within 4 weeks of collection, and in time for the updated data to be used to generate field listings for the next 4-weekly visit. Copies of the surveillance database will be made and frozen within three months after the completion of the fieldwork.

#### Participant flow & comparability of treatment arms

A flow diagram will be completed showing the number of zones, pregnancies, livebirths, neonatal deaths and loss to follow-up in the intervention and control arms, together with a map showing the locations of the intervention and control zones. Intervention and control zones will be compared with respect to the following variables: neonatal mortality rate, the percentage of skilled attendants at delivery and percentage of deliveries occurring in health facilities in 2007 (baseline); level of education of mothers, their ethnic group of origin, marital status and parity, and occupation (used as proxy indicator for the level of income), since these are known either to be related to the neonatal mortality rate or to effect peoples' knowledge, attitudes and practices on neonatal care. No statistical significance tests will be carried out on these comparisons [14,16]. However, analyses will be carried out both including and excluding these potential *a priori *confounders.

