#### Intention-to-treat analyses

The primary analysis for each outcome will be intention-to-treat, where intention to treat is defined by a woman's zone of residence. All analyses will account for the cluster-randomised design using random effects logistic regression and will be carried out both with and without adjustment for potential confounders (see above); individual-level methods are statistically more efficient than cluster-level methods, and are preferred when a large number of clusters have been randomised, as is the case in this trial, as they readily allow adjustment for covariates [16]. Quadrature checks will be carried out to confirm the reliability of the results; should these fail generalized estimating equations (GEE) and robust standard errors will be used instead [16]. The estimated effect of the intervention will be presented as a relative risk together with a 95% confidence interval. The intraclass correlation (ICC) and coefficient of variation (k) will be reported. Random-effects logistic regression will also be used to explore whether there are any differences in impact of the intervention: between facility- and home-based deliveries; between urban and rural areas; and between the four zones included in the pilot and the other intervention zones.

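### The covariate list for the care-practice primary outcomes omits the zone's own 2007 level of the practice, so where that level was recorded the adjusted intervals are probably wider than they need be

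*Protocol article*

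**What the plan says.** The Protocol article, section Impact evaluation, states: "The primary outcomes are all cause neonatal mortality and key care practices". The section Participant flow & comparability of treatment arms then gives one list of variables. Its zone-level part is the neonatal mortality rate, "the percentage of skilled attendants at delivery and percentage of deliveries occurring in health facilities in 2007 (baseline"). Its maternal part is "level of education of mothers, their ethnic group of origin, marital status and parity, and occupation". The same section says that "analyses will be carried out both including and excluding these potential" confounders. It gives two reasons for the choice: a known relation to neonatal mortality, or an effect on knowledge, attitudes and practices in newborn care.

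The section Intention-to-treat analyses applies this list to every outcome: "All analyses will account for the cluster-randomised design using random effects logistic regression", and these analyses "will be carried out both with and without adjustment for potential confounders", with a reference back to the list.

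On the source of the practice data, Impact evaluation says of the surveillance forms: "These forms were revised to ensure that they capture data on practices promoted by the Newhints intervention". It gives no date for the revision. The section Data Management dates the surveillance database from 2000 and adds that it was modified to take in new forms developed for the trial.

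**The concern.** For an outcome that varies between zones, the zone's earlier level of the same outcome is usually the best single predictor available. The list uses this device for mortality, skilled attendance and facility delivery, but not for breastfeeding, bathing, thermal care or similar practices, although practices are also primary.

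The choice is uneven. Mortality gains almost nothing from its own baseline, because one year's zone rate is mostly sampling noise at the protocol's ICC. Care practices plausibly cluster more strongly, and there the device could help. What is at stake is the precision of the adjusted practice comparisons, and the correction of a chance baseline difference in a practice that neither the design nor the listed covariates capture.

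**Working it through.** **Inputs from the protocol.** 98 zones, 49 per arm; 15,200 livebirths; baseline neonatal mortality 31 per 1000; mortality ICC 0.0007256; 5% level (taken as two-sided).

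**The plan's own figure.** Births per zone: m = 15,200 / 98 = 155.1. Design effect: 1 + (155.1 − 1) × 0.0007256 = 1.112. For 0.031 against 0.02325 (a 25% reduction) at 80% power, the individually randomised total is 13,792, and 13,792 × 1.1118 = 15,334. The stated 15,200 is within 1% of this. Power at 15,200 comes to 79.7%, 92.4% and 59.5% for reductions of 25%, 30% and 20%, against the stated 80%, 93% and 60%. The sample size reproduces and the present point does not affect it.

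**Inputs the protocol does not give (assumed).** Care-practice ICC, ρ: 0.02 to 0.05. Correlation of true zone levels between 2007 and the evaluation period, r: 0.5 to 0.85. About 155 births per zone in each period. Prevalence 50% for the illustration in percentage points.

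**Step 1: reliability of a zone's one-year level**, mρ / (1 + (m − 1)ρ).
- ρ = 0.0007256 (mortality): 0.1125 / 1.112 = 0.10
- ρ = 0.02: 3.10 / 4.08 = 0.76
- ρ = 0.05: 7.76 / 8.71 = 0.89

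**Step 2: interval width with the baseline covariate, relative to no zone-level baseline covariate**, √(1 − (r × reliability)²). This is an approximation on zone means, not on the logistic scale.

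| ρ | r = 0.5 | r = 0.7 | r = 0.85 |
|---|---|---|---|
| 0.02 | 7.5% narrower | 15.3% narrower | 23.7% narrower |
| 0.05 | 10.5% narrower | 21.8% narrower | 34.7% narrower |

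At the mortality ICC the ratio lies between 0.996 and 1.00 for r from 0.3 to 0.9, so there is practically no gain.

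**Step 3: in percentage points.** At prevalence 50% and ρ = 0.05, with 7,600 births per arm, the half-width is 1.96 × √(2 × 0.25 × 8.71 / 7,600) = 4.69 points. At r = 0.7 it becomes 4.69 × 0.782 = 3.67 points.

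**Step 4: gain beyond the covariates already listed.** Steps 2 and 3 compare with a model that holds no zone-level baseline value. The planned adjusted model already holds three such values and five maternal characteristics. The further gain depends on the partial correlation of zone means, with width ratio √(1 − partial²):
- 0: 1.00, or √(96/95) = 1.005 after losing one degree of freedom
- 0.2: 0.98 (2% narrower)
- 0.4: 0.92 (8% narrower)
- 0.6: 0.80 (20% narrower)

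**The case against.** The strongest reply is that the benefit may be nil and that the data may not exist. The surveillance was set up for a vitamin A and maternal mortality trial. The forms were revised so as to capture the promoted practices, which suggests that the older forms did not capture all of them, and some forms were new. The only pre-trial zone data that the article uses are mortality and place or attendance of delivery. This stands: 2007 practice data are plausible but not shown, so the recommendation must be conditional.

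It also stands that 8% to 35% is not the gain over the planned adjusted model. That gain is the Step 4 figure, and its range includes zero.

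A reader might infer that the list was drawn up for mortality alone. The document does not support this: its rationale also names effects on newborn care practices, and facility delivery, a promoted behaviour, already has its own 2007 level. A reader might also infer that the design leaves practices unbalanced apart from mortality and place of delivery. The Randomisation section describes 10 strata that separate four large towns from the remaining districts, which also balances geography and town versus rural setting.

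Finally, it can be said that outcome-by-outcome covariates belong in an analysis plan. That would hold if the protocol had left the list open. It instead names the variables, calls them a priori confounders and applies them to all analyses, so this is a stated choice.

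**Conclusion.** The point holds as a conditional improvement in precision, of minor severity. The single list gives mortality, skilled attendance and place of delivery their own 2007 zone level and gives newborn care practices none. Where a practice was recorded in 2007, its adjusted interval is probably wider than necessary, and any chance baseline difference beyond what the strata and listed covariates capture stays uncorrected.

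The size rests on an ICC and a correlation over time that the protocol does not give: about 8% to 35% narrower than with no zone-level baseline covariate, and about 0% to 20% narrower than the planned adjusted model for partial correlations from 0 to 0.6.

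A reader might go further and infer biased practice results, or certain loss of precision. Neither follows. Zones were randomised, so omitting a baseline covariate does not bias the comparison, every outcome is also analysed without adjustment, and the loss depends on data whose existence is not shown.

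**What to change.** In Participant flow & comparability of treatment arms and in Intention-to-treat analyses, provide that, for each key care practice that the surveillance recorded in 2007, the zone's 2007 level of that practice is added to the baseline comparison and to the adjusted model for that practice. Keep the present list for all other practices, and state which practices have no 2007 value.

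Calendar 2007 is the plan's own baseline year. It ends before the volunteers' first training in February 2008 and overlaps the community-leader meetings of December 2007 and January 2008 by one month at most. A cutoff at the February training would admit both months of those meetings, which took place only in intervention zones.

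Cost: one zone-level summary per practice from the existing database, where the practice was recorded, and one covariate per model. The covariate set will differ between practices. If the added covariate proves uninformative, the price is about one degree of freedom among 98 zones, or about 0.5% in interval width.

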#### Intention-to-treat analyses

The primary analysis for each outcome will be intention-to-treat, where intention to treat is defined by a woman's zone of residence. All analyses will account for the cluster-randomised design using random effects logistic regression and will be carried out both with and without adjustment for potential confounders (see above); individual-level methods are statistically more efficient than cluster-level methods, and are preferred when a large number of clusters have been randomised, as is the case in this trial, as they readily allow adjustment for covariates [16]. Quadrature checks will be carried out to confirm the reliability of the results; should these fail generalized estimating equations (GEE) and robust standard errors will be used instead [16]. The estimated effect of the intervention will be presented as a relative risk together with a 95% confidence interval. The intraclass correlation (ICC) and coefficient of variation (k) will be reported. Random-effects logistic regression will also be used to explore whether there are any differences in impact of the intervention: between facility- and home-based deliveries; between urban and rural areas; and between the four zones included in the pilot and the other intervention zones.

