### Overview of Trial Design

The Newhints intervention is being evaluated through a cluster randomised controlled trial design. The clusters are Newhints zones which correspond to supervisory units of about 8-12 CBSVs. There are 98 Newhints zones in total; 49 zones randomised for implementation of the Newhints intervention, with the other 49 zones acting as controls. The trial planning started in October 2006. The Newhints intervention was developed and fully implemented in the intervention zones by the end of 2008. Impact data on neonatal mortality and newborn care practices is being collected through ongoing surveillance of all women of child-bearing age and their infants in the trial area, and will be based on approximately 15,000 babies born from 1 January 2009. Detailed process, cost and cost-effectiveness evaluations are also being carried out. Data collection is expected to be completed in April 2010 and analysis will take place throughout 2010.

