### Randomisation

Meetings were held in each district in November 2007 to introduce the Newhints trial to all CBSVs, to explain the proposed randomization process and to obtain their cooperation and support for this; 686 CBSVs (91%) attended. Forty-nine zones were then selected at random for implementation of the Newhints intervention, with the other 49 zones acting as control. This was carried out by an independent epidemiologist using restricted stratified randomisation to ensure balanced numbers of intervention and control zones in each of 10 strata. These were the four large towns (Kintampo, Nkoranza, Techiman and Wenchi) and the six districts (Kintampo North, Kintampo South, Nkoranza, Tain, Techiman and Wenchi) minus these towns; note this took place before Nkoranza was divided into two districts, Nkoranza North and Nkoranza South. Restricted randomisation used available surveillance data to ensure that intervention and control arms were also balanced with respect to the following criteria: absolute differences of less than 2/1000 live births for neonatal mortality rates, less than 2.5% for the percentage of deliveries in a health facility, and less than 2.5% for the percentage of deliveries in a private hospital, in each of 2004, 2005 and 2006. An additional selection criterion was to ensure that the 4 pilot zones (which had been chosen at random) were allocated to the intervention group.

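### Neither version of the planned model includes the 10 randomisation strata, and neither is named primary; the precision cost is small for mortality but could be larger for care practices

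*Protocol article*

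**What the plan says.** **Allocation.** The Randomisation section of the protocol article describes "restricted stratified randomisation to ensure balanced numbers of intervention and control zones in each of 10 strata". The strata are the four large towns and the six districts minus those towns. Allocation was further restricted so that the arms were close on three variables in each of 2004, 2005 and 2006: neonatal mortality rate (NMR), percentage of facility deliveries and percentage of private-hospital deliveries.

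**Model.** Under Intention-to-treat analyses, the clustered design is accounted for "using random effects logistic regression and will be carried out both with and without adjustment for potential confounders". The section points back to the list under Participant flow & comparability of treatment arms. That list opens with "neonatal mortality rate, the percentage of skilled attendants at delivery and percentage of deliveries occurring in health facilities in 2007 (baseline") and continues with maternal education, ethnic group, marital status, parity and occupation. It says that analyses will be run with and without these variables.

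**Outcomes.** Impact evaluation names two kinds of primary outcome: all-cause neonatal mortality and key care practices.

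**Planning figures.** The Sample size section gives powers "using the baseline neonatal mortality rate (NMR) of 31 per 1000 live births" and an "intraclass correlation coefficient (ICC) of 0.0007256".

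**The concern.** There are two separate points.

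First, stratified allocation removes between-stratum differences from the comparison of arms. A model without strata does not use this: its zone random effect absorbs the between-stratum variation and carries it into the standard error of the arm effect. Inference remains valid but can be conservative, with intervals wider than necessary and some power lost. The loss depends on how far zones differ between strata. Place of delivery and newborn care may well differ between towns and rural districts. The plan treats such differences as worth attention, since it restricts on place of delivery and explores urban against rural effects.

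Second, each primary outcome will have two results, without and with covariates, and the article does not say which one answers the primary question. If the two fall on either side of the 5% level, nothing in the text settles which is the trial's result. The question recurs for every care practice.

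**Working it through.** **1. What each version contains**

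| Design variable | Unadjusted version | Adjusted version |
|---|---|---|
| 10 strata | no | no |
| NMR | no | yes, 2007 value |
| % facility delivery | no | yes, 2007 value |
| % private-hospital delivery | no | no |
| 2004-2006 values of the three restriction variables | no | no |

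Two of the three restriction variables are therefore in the adjusted version, for a different year. The strata are in neither.

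**2. Reproducing the planned power**

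Inputs from the article: 15,200 live births, 98 zones, 31 per 1000, ICC 0.0007256, 5% level (two-sided assumed).

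- Births per zone: m = 15,200/98 = 155.1.
- Design effect: DE = 1 + (m − 1) × ICC = 1 + 154.1 × 0.0007256 = 1.112.
- Effective number per arm: 7,600/1.112 ≈ 6,836.
- Two-proportion power for 0.031 against 0.02325: 79.7%. The article states "a total sample size of 15,200 livebirths would have 80% power to detect a 25% reduction in NMR at the 5% significance level".
- Reductions of 30% and 20% give 92.4% and 59.5%. The article states "93% power to detect a 30% reduction and 60% power to detect a 20% reduction".

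The planning figures reproduce. The article defines the ICC as between-zone over total variation, so it includes any between-stratum part.

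**3. Mortality: cost of omitting the strata**

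Let f be the share of between-zone variance that the strata explain. The article does not give f, so the whole range is shown. With strata in the model, DE(f) = 1 + (m − 1) × ICC × (1 − f), and the SE ratio without/with strata is √(1.112/DE(f)).

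| f | DE(f) | SE ratio | Power, 25% reduction |
|---|---|---|---|
| 0 | 1.112 | 1.000 | 79.7% |
| 0.25 | 1.084 | 1.013 | 80.7% |
| 0.50 | 1.056 | 1.026 | 81.7% |
| 0.75 | 1.028 | 1.040 | 82.7% |
| 1 (ceiling) | 1.000 | 1.054 | 83.7% |

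At a relative risk of 0.75 the 95% interval is 0.61 to 0.92 without strata and 0.62 to 0.91 at the ceiling.

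A simulation checked the direction. It used a linear model on zone rates, 4,000 runs per setting, and assumed stratum sizes of nine strata of 10 zones and one of 8. For f = 0, 0.5 and 1, type I error without strata was 5.1%, 3.9% and 3.6%. With strata it was 5.0%, 4.3% and 4.5%. The Monte Carlo standard error at 5% is √(0.05 × 0.95/4000) ≈ 0.3 percentage points.

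**4. Care practices: illustration under assumptions**

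The article gives no ICC for any practice. Assume 0.02 or 0.05, f of 0.25 or 0.50, m = 155.1 and no covariates. Actual type I error is 2 × (1 − Φ(1.96 × SE ratio)).

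| ICC | f | DE total | DE within strata | SE ratio | Actual type I error |
|---|---|---|---|---|---|
| 0.02 | 0.25 | 4.08 | 3.31 | 1.11 | 3.0% |
| 0.02 | 0.50 | 4.08 | 2.54 | 1.27 | 1.3% |
| 0.05 | 0.25 | 8.71 | 6.78 | 1.13 | 2.6% |
| 0.05 | 0.50 | 8.71 | 4.85 | 1.34 | 0.9% |

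**5. Does the single baseline year matter for mortality?**

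A zone expects 155.1 × 0.031 = 4.8 deaths a year. Reliability of the zone rate over y years is ICC·p(1−p) / [ICC·p(1−p) + p(1−p)/(155.1·y)], which is 0.10 for one year and 0.31 for four. Taking these as the most that adjustment could remove from the between-zone variance, DE falls to 1.101 or 1.077, and the SE shrinks by about 0.5% or 1.6%. Pooling 2004-2007 therefore gains about 1%.

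**The case against.** **This is a journal article.** Exact model terms and the lead estimate are often left to an analysis plan, which is not shown here and may settle both points. The covariate list is also headed as potential confounders rather than design variables, and the text does promise to account for the clustered design. This deserves weight, but the article does not defer the matter: it states how the design is handled (a random effect), lists the covariates and commits to both versions. The point rests on what is written.

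**The restriction variables.** A reader might infer that the model ignores them altogether. It does not: 2007 NMR and percentage of facility deliveries are in the adjusted version. Only private-hospital delivery and the 2004-2006 values are absent.

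**The size.** A reader might also infer that the intervals are certainly too wide, and by a third. The article gives no share of variance explained by the strata, so for mortality the excess may be zero. The 11 to 34% range rests on assumed ICCs and shares and describes only the version without covariates. The adjusted version includes facility delivery, skilled attendance, education, ethnic group and occupation, which plausibly carry much of the town-rural difference. No figure is available for that version.

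**Selective reporting.** Both versions are promised with a pre-listed covariate set, so this is not an open search over models. That limits the concern, but it does not say which result is primary.

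**Conclusion.** The point holds in a limited form. The strata used to randomise are in neither planned version, and no version is primary for any outcome.

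The direction of any error is conservative. Nothing here suggests bias or an inflated false-positive rate. For mortality the standard error is 0 to 5.4% too wide, worth at most 4 percentage points of power (79.7% against 83.7%). That bound uses the planning ICC and would rise if the realised ICC were larger. The simulation behind the direction is a linear approximation to the logistic model.

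For care practices a materially larger loss is possible but not demonstrated, for the reasons given above. The use of 2007 alone as the baseline year is not a defect of consequence for mortality.

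The missing designation of a primary version is the firmer half of the point, because it depends on no assumed quantity. The change is worth making because it is specific and nearly free.

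**What to change.** For each primary outcome, name one primary model: arm, fixed effects for the 10 strata, and a zone random effect. Define the strata as they stood at randomisation, when Nkoranza was still one district. Zone-level pre-intervention rates of the restriction variables (NMR, % facility delivery, % private-hospital delivery) may be added but are optional. State that the other version is supportive, and use the same rule for every care practice.

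The cost is analysis-plan wording. Each zone's stratum is known from the allocation, and 2004-2006 surveillance data were used for the restriction. The strata take 10 − 1 = 9 degrees of freedom out of 98 zones; three baseline rates bring this to about 12. If the strata explain nothing, the loss from those degrees of freedom is negligible: in the simulation with f = 0, power was 80.2% without strata and 80.1% with them.
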